#### *Exit survey*

The patient health facility exit survey will be administered to patients at all tertiary and secondary health facilities, and a corresponding sample of 8 dispensaries in both the Kilombero district and Same district. As each of these districts has 8 health centres, dispensary sampling will be matched by randomly selecting 1 dispensary from each ward containing a health centre.

The patient exit survey will be delivered at health facilities to adult patients seeking outpatient care. Target sample size was designed to be representative of patents visiting the health facilities for outpatient care for all conditions included NCDs. Hospital and health centre outpatient clinics typically designate one day per week as an ‘NCD day’, when a medical officer is assigned to be available to provide outpatient NCD care. As such, for each sampled hospital and health centre, the exit surveys will be delivered on one health facility NCD day to ensure that sufficient numbers of patients with NCDs can receive the questionnaire, and on one clinic day not designated for NCD care so as to also collect a more typical sample of people seeking outpatient care. Some rural health facilities, especially dispensaries which might not offer an NCD clinic day, might have low numbers of patients specifically visiting for chronic disease care, but this is representative of the typical clinical makeup and should be measured.

Rather than random or systematic random sampling, this study will use the more operationally efficient method of selecting and recruiting patients based on the order in which they enter the consultation room. As demonstrated by Geldseltzer et al. (2016), sampling patients as they enter the consultation room is advantageous as it is more efficient and simple to implement than random sampling approaches, and it minimises the bias of consultation length that is associated with sampling patients as the exit the consultation room [10].

It is expected that with 2 field workers per health facility, 36 patients can be interviewed per day at hospitals and health centres, while 1 one field worker is expected to be able to interview 12 patients per day at each sampled dispensary. If patient volume is too low to meet this daily requirement, field workers will return later to the same facility to ensure the sample size is reached. As such, across both districts, we are anticipating a total sample size of 1,632 for the exit survey (Table 1), generously exceeding the minimum sample size that was previously indicated. Participants will be recruited while waiting to enter the consultation room, and the research assistant will administer the questionnaire after the participants has seen the clinician so as to avoid disrupting the work flow at the clinic.

The questions asked in the exit survey will mostly be the same as those asked in the household survey, so that household survey respondents will serve as the general population with which people accessing NCD care can be compared. However, in the exit surveys, additional questionnaire items will be included relating to the specific services being utilised on the day of the health facility visit. The questionnaire will take on average 20 minutes to complete. If during the piloting phase the questionnaire takes too long to complete, we will reduce the number of questions asked from the accepted survey, prioritizing questions that best reflect the explicit research questions.

**Table 1: Sample size and sampling strata.** Sample size calculated based on a hypertension prevalence of 19.9% (95% CI: 17.1-22.9) for rural Tanzania [11], population estimates from the Tanzania 2012 census, and a benchmark mean annual household health expenditure of 30,000 Tanzanian shillings by using a modified Cochran sample size calculation.

| **Study Type** | **Sample Size** | **Strata** |
| --- | --- | --- |
| Exit Interviews |  | Kilombero District:   - 18 health facilities |
|  | 72 per hospital | - 2 hospitals |
|  | 72 per health centre | - 8 health centres |
|  | 12 per dispensary | - 8 dispensaries |
|  |  | Same District:   - 18 health facilities |
|  | 72 per hospital | - 2 hospitals |
|  | 72 per health centre | - 8 health centres |
|  | 12 per dispensary | - 8 dispensaries |
|  | **Total: 1,632** | **Total: 36 health facilities** |
| Household Survey |  | Kilombero District: |
|  | 15 households | Ifakara town |
|  | 15 households per village | Sample of 25 villages |
|  |  | Same District: |
|  | 15 households | Same town |
|  | 15 households per village | Sample of 25 villages |
|  | **Total: 790 households** | **Total: 52 towns/villages** |

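### The exit survey is called representative of all outpatients, but its sample is enriched for NCD-day patients, ignores patient volume, and takes dispensaries only from wards with a health centre

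*Protocol*

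**What the plan says.** All of the following is in the protocol, section Exit survey, including its Table 1.

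- **Target:** "Target sample size was designed to be representative of patents visiting the health facilities for outpatient care for all conditions included NCDs".
- **NCD day:** "Hospital and health centre outpatient clinics typically designate one day per week as an ‘NCD day", in the protocol's words.
- **First survey day (every hospital and health centre in the sample):** "the exit surveys will be delivered on one health facility NCD day to ensure that sufficient numbers of patients with NCDs can receive the questionnaire".
- **Second survey day:** "on one clinic day not designated for NCD care so as to also collect a more typical sample of people seeking outpatient care".
- **Quotas:** the expectation is that "36 patients can be interviewed per day at hospitals and health centres". Table 1 sets 72 per hospital, 72 per health centre and 12 per dispensary, without regard to attendance. Where attendance is too low, "field workers will return later to the same facility to ensure the sample size is reached".
- **Facilities:** all hospitals and health centres in both districts are taken. The 8 dispensaries per district come from "randomly selecting 1 dispensary from each ward containing a health centre".

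The protocol mentions neither weights nor the recording of facility attendance. The section Analytical Methods describes the exit survey as one given to people accessing NCD services, which does not match the all-conditions target above.

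**The concern.** A sample represents all outpatients without weights only if each outpatient visit has about the same chance of selection. Three features prevent that here:

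1. The NCD day is one day of the clinic week but supplies half of the interviews at hospitals and health centres.
2. A fixed quota gives a patient at a quiet facility a higher chance of selection than a patient at a busy one. Returning until the quota is filled keeps it so.
3. Dispensaries in wards without a health centre cannot be selected at all.

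The protocol itself implies that case mix differs by day, because it uses the NCD day to find NCD patients and calls only the other day more typical. If the representativeness statement is carried into reports, unweighted costs, insurance mix, willingness-to-pay or distance for outpatients in general would be read as district figures when they are not.

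**Working it through.** **Inputs from the protocol (Exit survey, Table 1).** Two districts, each with 2 hospitals, 8 health centres and 8 sampled dispensaries; 72, 72 and 12 interviews per site; 36 interviews per day at hospitals and health centres; typically one NCD day per week.

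**Step 1: reproduce the total.** 2 × (2 × 72 + 8 × 72 + 8 × 12) = 2 × 816 = 1,632, as stated.

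**Step 2: planned share from the NCD day.** There are 20 hospitals and health centres. NCD-day interviews are 20 × 36 = 720, out of 20 × 72 = 1,440 (50%), or 720/1,632 = 44.1% of the whole exit sample. Dispensaries give 16 × 12 = 192, or 11.8%. This is the planned split; the protocol does not say on which type of day a return visit would fall.

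**Step 3: share of visits that the NCD day would supply.** Let D be clinic days per week and r the NCD-day volume relative to another day. Neither is stated, so both are assumed: D = 5 to 7, r = 1 or 2. The natural share is s = r/(r + D − 1), the over-representation is 0.5/s, and the Kish design effect of weights that restore s is 2 × [s² + (1 − s)²].

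| D | r | s | Over-representation | Design effect | Effective n of 1,440 |
|---|---|---|---|---|---|
| 5 | 1 | 20.0% | 2.5 | 1.36 | 1,059 |
| 6 | 1 | 16.7% | 3.0 | 1.44 | 997 |
| 7 | 1 | 14.3% | 3.5 | 1.51 | 954 |
| 5 | 2 | 33.3% | 1.5 | 1.11 | 1,296 |
| 6 | 2 | 28.6% | 1.75 | 1.18 | 1,217 |
| 7 | 2 | 25.0% | 2.0 | 1.25 | 1,152 |

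**Step 4: what this does to an unweighted all-outpatient figure.** Take the NCD share at hospitals and health centres. With shares p₁ on the NCD day and p₀ on other days (assumed), the sample shows (p₁ + p₀)/2 and the truth is s·p₁ + (1 − s)·p₀.

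| p₁ / p₀ | Sample | Truth, r = 1 (D = 7 to 5) | Truth, r = 2 (D = 7 to 5) |
|---|---|---|---|
| 50% / 10% | 30% | 15.7–18.0% | 20.0–23.3% |
| 30% / 20% | 25% | 21.4–22.0% | 22.5–23.3% |
| 30% / 30% | 30% | 30% | 30% |

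The distortion runs from nothing, if case mix does not vary by day, to about 14 percentage points in these rows (30% against 15.7%).

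**Step 5: analyses split by NCD status.** With p₁ = 50%, p₀ = 10%, D = 5 and r = 1, the NCD day accounts for 0.10/0.18 = 56% of NCD visits, and for 0.25/0.30 = 83% of sampled NCD patients. The day mix within NCD patients still shifts. It matters only if NCD patients who come on the NCD day differ from those who come on other days.

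**Step 6: dispensaries.** A weight is the inverse of a selection probability. For dispensaries in wards without a health centre that probability is zero, so no weight exists. The documents do not allow the size of the effect to be calculated.

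**The case against.** The strongest reply has four parts.

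- **The enrichment is deliberate, disclosed and sensible.** A study of access to NCD care needs enough NCD patients. This stands: the design choice is not at fault, only the claim placed beside it.
- **The planned contrasts mostly avoid the problem.** Analytical Methods compares NCD patients in care with household respondents not in care, and reports willingness-to-pay separately for NCD patients, non-NCD patients and household respondents. It announces no mean over all outpatients. A reader might infer that the study's pooled estimates are biased; the protocol does not support that, because it specifies no such estimate. What remains is the general descriptive analysis of the exit data, and the distance models, which might pool visits.
- **Weights may be in an SAP that is not shown.** This also stands, and their absence from the protocol is not the finding. But weights need attendance counts, which the protocol does not plan to collect and which may be hard to obtain after fieldwork.
- **The dispensary restriction has a purpose and limited reach.** It matches dispensaries to health centres by ward, and dispensaries are 11.8% of interviews. A reader might infer that the excluded wards have the thinnest access, or that their residents are missing from the study. The documents do not say the first. The second is wrong as stated, because the household survey draws villages at random without this restriction.

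Hospitals and health centres are all included, so no selection among them arises; the imbalance there lies in day type and volume.

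**Conclusion.** The point holds in a limited form. The exit sample is not self-weighting and cannot be called representative of outpatients for all conditions. That half of the hospital and health-centre quota comes from the NCD day, that quotas ignore volume, and that some dispensaries have no chance of selection all follow from the protocol alone.

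The 1.5- to 3.5-fold over-representation rests on the assumed 5- to 7-day week and an NCD day one to two times as busy as others. The effect on any particular estimate also depends on case mix, and the effect of equal quotas on facility volumes; the protocol gives neither. The consequence is conditional: an unweighted all-outpatient figure would be tilted towards NCD-day patients and low-volume sites, while analyses within NCD or non-NCD visits are less affected. The documents do not establish that any result the protocol names will be biased.

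**What to change.** 1. **Record attendance and weight.** During fieldwork, take from each facility's register the outpatient attendance for the survey day and for the week. Weight any all-outpatient exit-survey estimate by day type and facility volume. At a hospital or health centre, the weight is NCD-day attendance in the week divided by NCD-day interviews, and attendance on the remaining days divided by interviews on the other day. Analyses stratified by NCD and non-NCD visit may stay unweighted if they are labelled so.
2. **Correct the claim.** Drop the word *representative* for unweighted figures and describe the sample as NCD-enriched. Bring the description of the exit survey in Analytical Methods into line with the all-conditions target.
3. **Limit the dispensary conclusions** to wards with a health centre.

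The cost is one register count per visit and some text. Day-type weights carry a design effect of about 1.1 to 1.5 under the assumptions above (1,440 interviews worth about 1,296 to 954). Volume weights add a further loss that cannot be quantified without attendance data. Redrawing the dispensaries from all wards is optional: it would widen the frame with the same number of sites, but gives up the stated matching to health centres and may add travel.

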### Sampling Strategy and Sample Size

#### *Household survey*

We will conduct a household survey to collect information on household demographic and economic characteristics, health insurance and social protection, chronic illness, healthcare access and utilisation, household health expenditure, out of pocket payments for health care, and coping strategies to deal with diseases. In order to answer the key research question, information will be collected regarding direct and indirect household out-of-pocket expenditure (OOPs) on healthcare, how the household pays for their OOPs or social health protection premiums, economic productivity loss due to illness, recent healthcare utilisation, and the role of one’s social network in coping with illness. For respondents that accept, we will also measure blood pressure and random blood sugar to quantify undiagnosed and untreated hypertension and possible diabetes in the population. We will counsel patients with results outside of the normal range of the importance of following up with a healthcare provider to formally diagnose and initiate treatment if needed.

Using a stratified sampling approach, a household survey will be delivered throughout Kilombero and Same districts. In order to detect associations with the primary outcome of household health expenditure (power of 0.80, significance level of 0.05), a minimum sample size of 202 households per district is required. To calculate the minimum sample size, a household health expenditure of 30,000 Tanzanian shillings was used as a benchmark; corresponding to the cost of enrolling a household in the iCHF. However, in order to also answer research questions associated with our secondary objectives, we will seek a total sample size of 390 households per district.

As such, in each of Kilombero and Same district, 15 households from each district’s only town (Ifakara and Same, respectively), and 15 households from a random selection of 25 other villages will be sampled (Table 1).

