### Analytical Methods

By delivering a household survey to the general populations of Kilombero and Same, and an exit survey to people accessing NCD services, we will be able to comparatively analyse the specific challenges and coping mechanisms that people living with NCDs face in accessing services, in relation to the general population.

The data collected from the household survey and exit survey will first be analysed using descriptive statistics to investigate the burden of OOPs and economic losses associated with living with hypertension and/or diabetes, and to determine how much households spend upon the direct and indirect costs of accessing NCD care. General hypotheses related to the geographic and economic accessibility of health care, such as whether distance from a health facility is associated with direct and indirect healthcare costs, and whether distance from a health facility moderates the association between social health protection and household health expenditure, will be explored using linear mixed models and analyses of variance.

We will quantify the proportion of the household survey respondents who were hypertensive or diabetic, and not aware of their condition or not enrolled in care. We will then use univariate and multivariate logistic regression analyses to identify differences between the household respondents with an NCD who are not enrolled in care and NCD patients from the exit interviews who are enrolled in care. We will quantify systematic and individual characteristic predictors of willingness-to-pay for NCD care and social health protection schemes for people in care for non-NCD reasons, for NCD reasons, and household respondents.

A regression model will then be used to assess whether living with hypertension and/or diabetes is associated with financial hardship, and/or illness-related economic and productivity losses, using the indicators catastrophic health expenditure and impoverishment. An analysis of variance (ANOVA) of mean spending by revenue source will then be used to determine the relative importance of financial contributions from various household revenue streams to covering the costs of NCD care, such as:

- Earnings from work (informal or formal)

- Selling personal property (clothing, bicycle, furniture, etc.)

- Financial contributions from the social network (friends, family, neighbours, etc.)

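### The household minimum of 202 makes no stated allowance for sampling 15 households per locality, and the claim that the exit survey generously exceeds a minimum has no valid comparator

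*Protocol*

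**What the plan says.** In *Sampling Strategy and Sample Size*, under *Household survey*, the protocol sizes the survey to detect associations with the "primary outcome of household health expenditure (power of 0.80, significance level of 0.05") and concludes that "a minimum sample size of 202 households per district is required". The expenditure input is that "a household health expenditure of 30,000 Tanzanian shillings was used as a benchmark". The target is then raised to 390 per district, and the reason given is the secondary objectives. In each district 15 households come from the only town, and "15 households from a random selection of 25 other villages will be sampled"; Table 1 confirms that this means 15 in each village.

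The caption of Table 1 lists the inputs: "Sample size calculated based on a hypertension prevalence of 19.9% (95% CI: 17.1-22.9) for rural Tanzania", 2012 census populations, the expenditure benchmark and a modified Cochran calculation. The modification is not described.

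Under *Exit survey*, the planned numbers are 72 per hospital, "72 per health centre" and 12 per dispensary. The resulting total of 1,632 is described as "generously exceeding the minimum sample size that was previously indicated".

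*Analytical Methods* assigns the distance and cost hypotheses to linear mixed models and analyses of variance. It assigns the comparison of people in and out of care to "univariate and multivariate logistic regression analyses", and financial hardship to a regression model that is not specified further.

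**The concern.** Households in one village share prices, facilities and distance to care, so their health expenditure is likely to be correlated. Fifteen households from one village then carry less information about a district mean, or about a village-level characteristic, than 15 households drawn independently. A minimum that ignores this is too small for the power attached to it.

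The exit-survey sentence is a separate problem. It tells the reader that adequacy has been checked against a figure given earlier. If no such figure exists for that survey, nothing was checked.

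At stake is whether the stated power can be relied on, and whether an ethics committee or later reader is told that the exit survey is comfortably large when the protocol does not show it.

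**Working it through.** **The protocol's own figures**

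- Household target: (1 + 25) × 15 = 390 per district, as stated.
- Exit total: 20 × 72 + 16 × 12 = 1,440 + 192 = 1,632, as stated.
- The 202 cannot be reproduced from the stated inputs, because no standard deviation, effect size or margin of error is given. Cochran's formula, n = 1.96² × p(1 − p)/e² with p = 0.199, gives 245 at e = 0.05 and 202.4 at e = 0.055. The second matches, but 0.055 appears nowhere, and that formula has no power term. A one-sample test with standardised effect 0.20 gives (2.802/0.20)² = 196.2, rounded up to 197; that effect is not stated either. The 0.055 match suggests a simple-random-sampling formula without a design effect, but this is inference.

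**Allowing for clusters of 15 households**

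Assumptions: 202 gives exactly 80% power under simple random sampling; the test is two-sided at 0.05; the ICC values are illustrative, since the protocol gives none.

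- Design effect: DEFF = 1 + (15 − 1) × ICC
- Inflated minimum: 202 × DEFF, rounded up
- Power with n households: Φ(2.802 × √((n/DEFF)/202) − 1.960), where 2.802 = 1.960 + 0.842

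| Assumed ICC | DEFF | Inflated minimum | Power at 202 | Power at 390 |
| --- | --- | --- | --- | --- |
| 0.01 | 1.14 | 231 | 75% | 95% |
| 0.02 | 1.28 | 259 | 70% | 93% |
| 0.05 | 1.70 | 344 | 58% | 85% |
| 0.10 | 2.40 | 485 | 44% | 71% |

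Worked line at ICC 0.05: 202 × 1.70 = 343.4, so 344. At 202, √(1/1.70) = 0.767 and Φ(2.802 × 0.767 − 1.960) = Φ(0.189) = 0.575. At 390, 390/1.70 = 229.4, √(229.4/202) = 1.066 and Φ(2.986 − 1.960) = Φ(1.026) = 0.85.

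The ICC at which 390 gives exactly 80% is (390/202 − 1)/14 = 0.0665.

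**The exit-survey comparator**

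The only earlier minimum is 202 households per district. It concerns annual household expenditure in a general-population survey. The exit survey samples adult outpatients by order of entry to the consultation room, and its number follows from interviewer capacity: 36 a day on two days, or 12 at a dispensary. The two figures differ in sampling unit, population and survey, so one cannot show that the other is adequate, whatever the ICC.

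**The case against.** The strongest reply is that 202 is a floor and the survey will recruit 390. That stands, and it limits the point. A reader might infer that the household survey as fielded is underpowered. The protocol does not show this: 390 keeps 80% power up to an ICC of about 0.066, and every scenario in which it fails rests on an ICC that the protocol does not give. The undefined modification of Cochran's formula might also hide a cluster allowance. That cannot be excluded, but nothing in the text indicates one.

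A reader might go on to shrink the 1,632 exit interviews by a design effect for 72 patients per facility. The design does not support that as a general correction. Under *Exit survey*, all secondary and tertiary facilities in the two districts are taken, so for district-level estimates the hospitals and health centres act largely as strata; only dispensaries are sampled. Some clustering by survey day remains, and inference beyond these facilities would need facility effects, but one effective sample size would be misleading.

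It is also tempting to say that the results on distance will have standard errors that are too small. *Analytical Methods* assigns both distance hypotheses to linear mixed models and analyses of variance, and mixed models can carry locality or facility effects. For the logistic models the protocol is silent on variance estimation. It does not say that clustering will be ignored, and a statistical analysis plan that is not at hand may deal with it. That comparison also uses only people with an NCD, so its clusters are smaller than 15 or 72.

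One might defend the exit claim by saying that the Table 1 caption covers both surveys. It lists inputs but gives no exit-survey minimum, and none is stated before the sentence that relies on one.

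**Conclusion.** Two statements need correction. First, the protocol attaches 80% power to 202 households per district without any stated allowance for 15 households per locality. Under the assumptions above, that power is not reached at any positive ICC. The target of 390 repairs this up to an ICC of about 0.066, but the protocol does not present it as doing so. Second, the adequacy claim for the exit survey is unsupported because it has no valid comparator. This second conclusion needs no ICC.

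The design effect used is the one for a mean or for a characteristic shared by a whole locality; for predictors that vary within localities the loss would be smaller. It also treats the town, 15 of the 390 households, like a sampled village. Because 202 could not be reproduced, the power figures show the scale of the problem and are not exact properties of the design. The total of 1,632 is itself correct.

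**What to change.** - *Household survey*: state an assumed ICC with its basis, multiply the minimum by 1 + (15 − 1) × ICC (344 at 0.05, 485 at 0.10) and state the ICC range over which 390 suffices. Give the missing standard deviation, effect size or margin of error, so that 202 can be checked.
- *Exit survey*: delete the clause claiming that the minimum is exceeded, or replace it with an exit-survey minimum or precision statement that allows for clustering by facility and survey day.
- *Analytical Methods*: for the logistic care-engagement model, specify standard errors clustered on village or facility. A random intercept does not suit this model: everyone compared from a village is out of care and everyone from a facility is in care, so the outcome is constant within each cluster. For the financial-hardship model, either cluster-robust standard errors or a random intercept would do.

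This costs wording and a standard analysis option, with no additional interviews. The downside is a less favourable stated minimum and wider intervals.

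### Table 1 gives a household survey total of 790, but its own strata, the per-district target and the site count all give 780

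*Protocol*

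**What the plan says.** The Household survey subsection of the protocol states that "we will seek a total sample size of 390 households per district". It builds this up from 15 households in the single town of each district and "15 households from a random selection of 25 other villages will be sampled (Table 1").

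Table 1, printed under the Exit survey subsection, repeats the same strata for both districts. Each has one town with 15 households, and then "15 households per village" for a "Sample of 25 villages". The closing row gives two totals side by side: "Total: 52 towns/villages" and "Total: 790 households".

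For the primary outcome, household health expenditure, the Household survey text says that "a minimum sample size of 202 households per district is required", at power 0.80 and significance level 0.05.

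**The concern.** The household total in Table 1 should be the sum of fixed quotas listed directly above it, so it should match exactly. It does not, and it also disagrees with twice the per-district target in the text.

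The table is the only place where the protocol gives one combined household figure for the two districts. A reader who wants the planned size of the household survey will probably take it from there. A field team that fills every stratum exactly as specified would finish 10 households below that figure, with no stratum to which further households could be assigned. What is at stake is the internal consistency of the planned sample size, not the validity of any result.

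**Working it through.** **Inputs**

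- Districts: 2 (Kilombero and Same).
- Towns per district: 1, with 15 households (Household survey text and Table 1).
- Villages per district: 25, with 15 households each (Table 1).
- Target per district: 390 (Household survey text).
- Total sites: 52 (Table 1).
- Stated household total: 790 (Table 1).

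**Attempt to reproduce the stated total, by three routes**

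1. Strata: households per district = 15 + 25 × 15 = 15 + 375 = 390. Both districts: 2 × 390 = 780.
2. Text target: 2 × 390 = 780.
3. Site count: sites = 2 × (1 + 25) = 52, as stated; 52 × 15 = 780.

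All three give 780. The difference is 790 − 780 = 10 households, and 10 / 780 = 1.3%.

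**Could some other reading give 790?**

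- Different number of sites: 790 / 15 = 52.67, not a whole number.
- Different quota per site: 790 / 52 = 15.19, not a whole number.
- Larger town samples: 790 / 2 = 395 per district. With 25 × 15 = 375 from the villages, each town would need 395 − 375 = 20 households, against the stated 15.
- Non-response allowance: going from 780 to 790 would imply 1 − 780 / 790 = 1.3%. No such allowance is stated for the household survey.
- The village quota as 15 in total: read alone, the sentence in the text could mean 15 households across all 25 villages. That would give 15 + 15 = 30 per district, below the stated minimum of 202 and nowhere near 390. Table 1 says per village, and only that reading reaches 390.
- The sample-size calculation named in the table caption: the caption cites a modified Cochran method but gives no margin of error, so it cannot be shown to yield 790. The row in question in any case closes a list of quotas.

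**Are the other totals in the table sound?**

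- Exit interviews: 2 × (2 × 72 + 8 × 72 + 8 × 12) = 2 × (144 + 576 + 96) = 2 × 816 = 1,632, as stated.
- Health facilities: 2 × (2 + 8 + 8) = 36, as stated.
- Towns and villages: 52, as stated.

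Only the household total fails.

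**Effect on power**

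The stated minimum for both districts is 2 × 202 = 404. Then 780 / 404 = 1.93 and 790 / 404 = 1.96. Either total is nearly twice the minimum.

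**The case against.** The strongest reply is that this is a slip in one summary cell and changes nothing that will be done. The text and the table agree on the sites and on the households per site, and the text gives the resulting per-district target. The survey can be carried out without ambiguity, and a reader can correct the total from the rows above it. The gap is 1.3%, well inside what one would tolerate when checking a sample-size formula. Nothing in the Analytical Methods section depends on the planned total.

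Most of this stands, and it settles the weight of the point: minor. It does not remove the error. A tolerance for rounding or for variants of a formula has no place in a sum of whole-number quotas, which is either right or wrong.

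A reader might also infer something stronger: that response rate or completeness will be judged against 790, so that a fully completed survey would be reported as deficient. The protocol does not support this. It defines no response or completeness measure for the household survey and ties none to Table 1. Nor does the Research Ethics section single out 790 as the number to be approved; the same document also states 390 per district.

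**Conclusion.** The Table 1 household total is wrong as written. It overstates the planned sample by 10 households (790 against 780, 1.3%). The conclusion rests only on quotas stated in the protocol and on reading the village quota as 15 per village, which Table 1 states outright. The likeliest explanation is a typing or addition slip.

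The consequence is an inconsistent planned total and no more. Power for the primary outcome is not threatened, and the analysis is untouched. Nor should 780 be treated as a response-rate denominator. A response rate is normally taken over households approached or eligible, and the protocol does not say whether refusing households are replaced. If they were, completed interviews over 780 could reach 100% whatever the refusal rate. The figure of 780 measures attainment of the enrolment target only.

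**What to change.** Change the household total in Table 1 from 790 to 780, so that it agrees with the strata, the 52 sites and the target of 390 per district. If 790 was intended, state which strata hold the additional 10 households and amend the quotas and the per-district target in the Household survey text accordingly. The first option changes one number, and neither the design nor the analysis has to be altered.
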